#### Mental Health

Mental health will be assessed from the results of 2 questionnaires: the Positive and Negative Affect Scale (PANAS [52]) and the HADS [58], both of which are included in an item bank for cancer survivors [59]. The PANAS consists of 20 items that score on a 5-point Likert scale and has 2 subscales: positive and negative affect. The HADS consists of 14 items on a 4-point scale, has been validated for a Dutch-speaking population [60], and has previously been used to assess psychological distress in cancer patients [61]. Mental health will be assessed at T0a, T1, T2, and T3.

#### Perceived Ability to Work

The work ability score, which is assessed with the first question of the work ability index [62,63], will also be used as an outcome parameter. It asks: “Imagine that your working ability in the best period of your life is rated 10 points. How would you rate your working ability at the present moment?” It is assessed at T0b, T1, T2, and T3.

Working hours and the level of absenteeism are assessed with questions from the Trimbos and iMTA questionnaire on costs associated with psychiatric illness (TiC-P) [64]). These will be assessed at T0b, T2, and T3.

**Table 2 table2:** Assessments of outcome measures and potentially mediating factors.

Outcome Measures and Potentially Mediating Factors		Parameters	T0^a^	Mi/Mi’^b^	T1/T1’	T2/T2’	T3
Primary outcome	Fatigue severity	CIS fatigue severity subscale: 8 items on a 7-point Likert scale.	a, b	3,6,9	x	x	x
Secondary outcomes	Other dimensions of fatigue	CIS physical and cognitive fatigue and motivation subscales: 4 items for each subscale, all on a 7-point Likert scale.	b		x	x	x
	Affect	PANAS: 20 items on a 5-point Likert scale.	a		x	x	x
	Psychological distress	HADS: 14 items on a 4-point scale.	a		x	x	x
	Self-perceived ability to work	Work ability score: 1 item on a 0-10 numeric rating scale (NRS).	b		x	x	x
	Return to work and working hours	Adapted questions of the TiC-P.	b			x	x
Primary mediating factors	Mindfulness	Freiburg Mindfulness Inventory short form [65,66]: 14 items on a 4-point Likert scale.	b	3,6,9	x	x	x
	Physical activity (PA)	Accelerometer: ProMove 3D [52]. Both summative PA and daily PA decline will be considered.	b	3,6,9^c^	x		
	Sleep quality	Subjective Sleep Quality Scale [67]:15 items (yes/no), and 1 self-conceptualized item (yes/no) that translates into: “Did you use sleep medication?”	b	3,6,9	x	x	x
	Sense of control over fatigue	Self-Efficacy Scale [56]: 7 items on a 4-point Likert scale.	b	3,6,9	x	x	x
	Credibility and expectancy	Credibility and Expectancy Questionnaire [68]: 6 items of which 4 are on a 9-point Likert scale, and 2 items on a 0-100 NRS.	c, c’	1,2,4			
	Working alliance	Working Alliance Inventory short form [69,70]: 12 items on 5-point scale; subscales: goal, task, bond.		1,2,4			
Secondary mediating factors	Perceived physical activity	Four self-conceptualized questions on perceived activity volume, comparative volume, and satisfaction with volume.	b		x	x	x
	Self-efficacy on activities	Selected items from the self-efficacy scales of Bandura [71] and Rodgers [72,73]: 13 items on a 0-100 NRS; subscales: planning and coping.	b		x		
	Catastrophizing	Fatigue Catastrophizing Scale [74,75] 9 selected items on a 5-point Likert scale.	b		x		
	Fear of cancer recurrence	Two selected items on a 7-point Likert scale [76].	b		x		
	Causal attributions	One self-conceptualized open answer question that translates to: “What do you consider as the cause of your fatigue?”	b		x		

^a^Baseline assessment T0 consists of 3 time-points: T0a: before eligibility check, T0b: after inclusion, and T0c: after randomization. T0c’ is assessed after preferential allocation.

^b^Mi and Mi’ = assessments at week (i=) 1, 2, 3, 4, 6, 9 of the intervention

^c^All physical activity measurements are blind except for the experimental activity feedback condition at M3, M6, and M9. In the second semester, M3’, M6’, and M9’ do not include a physical activity measurement in the mindfulness condition.

**Table 3 table3:** Other assessments.

Demographics, medical history, and control factors	T0^a^	T1/T1’	T2/T2’	T3
Age, gender, education, family status, nationality, time since diagnosis, time since previous treatment, fatigue duration, psychological counseling in the past, comorbidity.	a			
Cancer type, cancer treatment, perceived life threat of cancer (7-point Likert scale), known heredity of cancer (yes/no/don’t know), former experience with attention focusing exercise (yes/no), religious beliefs, perceived social support (Multidimensional Scale of Perceived Social Support [77]: 12 items on a 7-point Likert scale).	b			
Medication use, substance use (caffeine, nicotine, alcohol, drugs), quality of life (1 item on a 0-10 NRS).	a	x	x	x
Pain intensity and limitations by pain (2 items on a 7-point Likert scale), body mass index.	b	x	x	x
Life events since previous assessment, professional help received for fatigue outside the scope of the study protocol.		x	x	x
Perceived effectiveness of the intervention (5 items of which 1 item 0-10 NRS and 2 yes/no questions), perceived social support in following the intervention (1-10 NRS).		x		
Social desirability: 6 selected items from the Balanced Inventory of Desirable Responding [78] on 5-point Likert scale.			x	

^a^Baseline assessment T0 consists of 3 time-points: T0a: before eligibility check; T0b: after inclusion; and T0c: after randomization.

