## Methods

### Design

A randomized controlled trial is performed including 3 parallel conditions: 2 experimental conditions (AAF and eMBCT) and a minimal intervention control condition. The intervention period is 9 weeks for all 3 conditions. Both experimental conditions are made as similar as possible in terms of time-investment and contact intensity with the therapist. Outcomes are self-reported and are Web-assessed at baseline (T0), 2 weeks post-intervention (T1), and at 6 months (T2) and 12 months (T3) after baseline. Figure 3 shows a schematic summary of the trial design.

The baseline assessment consists of 3 time-points: (1) T0a, the assessment to check eligibility; (2) T0b, the main baseline assessment taken after the eligibility check and informed consent, but naive of condition; and (3) T0c, directly after randomization for assessing the participant’s credibility and expectancy about the condition. All participants are invited to fill out short questionnaires in weeks 1, 2, 3, 4, 6, and 9 (Mi) of the intervention period in order to study mediation of the interventions.

After T2, patients in the control condition are offered 1 of the 2 experimental interventions, again in a research setting. Please note that the first 4 participants of this trial were randomized to 1 of the experimental conditions for the second semester, but to minimize dropout, all other patients will be allocated based on their own preference. During this second intervention period, these participants will again be assessed in weeks 1, 2, 3, 4, 6, and 9 (Mi’), the second week after the intervention (T1’), and 6 months after the second allocation (T2’). Participants in the control condition that are preferentially allocated to eMBCT after T2 do not wear the accelerometer during the second semester.

The protocol allows delay within the intervention period of a maximum of 2 weeks in case of, for example, illness or holiday. For all participants, the duration of their participation is approximately 12 months. Additional qualitative feedback will be obtained through explorative interviews with a subset of participants in the experimental condition shortly after T1 or T1’.

This trial was approved by the Twente Medical Ethical Committee (Enschede, the Netherlands) under number P12-26 and has been registered at The Netherlands National Trial Register under number NTR3483 [42].

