#### Pre-Analysis

##### Power Analyses

The sample size for analyses for data relating to the primary objective has been calculated for a repeated measures analysis of variance: based on an alpha of .05, a minimal detectable effect size of f2=.15, and a power of .80, a total number of 55 participants [80] is required in each group to answer the primary research question of this study in a statistically valid manner.

We expect to be able to include 330 eligible participants within a period of 2 years, based on a mean of 3.7 intakes per week for the eMBCT of the Helen Dowling Institute in 2011. An estimated attrition of 30% of the participants during both experimental interventions and 15% during the minimal intervention control condition [51] would leave us with 77 participants in each experimental group and 94 participants in the control group at T2. Again, we expect a dropout rate of 30% during the second semester. Such a dropout would leave a total of 110 participants completing each experimental intervention. Ten percent of the participants may have to be excluded from the analyses because of recurrence or diagnosis of metastasis. That would result in 198 participants that complete the full trial. We expect that this number will be enough for testing the 6 mediating factors or effect predictors: A classical, conservative power calculation (analysis of variance for testing 6 mediators or effect predictors with an intermediate effect size (f2=.08), corrected according to Bonferroni (alpha=.05/6), and at a power of .80 [81]) would result in approximately 254 participants being needed. We expect that the actual power when including 198 participants, and not the required 254 participants, will be great enough to detect up to 6 mediators or effect predictors with the use of Bayesian statistics [76]. Bayesian statistics allow analysis on small sample sizes [76,77], as more power can be generated with the use of prior information which is incorporated in the model that is being tested. Various papers describe comparisons between traditional null hypothesis testing and Bayesian estimation [82-85]. For this study, prior knowledge is available for many parameters, such as the effects of mindfulness in cancer survivors [23,25,66,86] and the role of working alliance in online interventions [87]. Examples of these methods can be found in both applied psychology and social science articles [88-92].

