**Figure 5 figure5:**
[figure not shown]
Simplified representation of a correlated growth model in which Iy and Sy represent the intercept and slope factors of the latent growth model of the outcome parameter, and Iz and Sz represent the latent growth factors of the mediator. H1-4 represent the 4 subhypotheses of Step 6. All indicators have been left out for clarity.

###### Step 7

The next step in studying potential working mechanisms is a single-step, multiple-mediation analysis using structural equation modeling [104-106]. By estimating such a model, we expect to obtain a comprehensive model for all the working mechanisms of the intervention. It should be noted that this model assumes that an intervention works in the same way for all participants in a particular group [107]. Again, data from both semesters will be used.

A separate model will be tested for each intervention. Each model will have the following paths (Figure 6), where X=independent variable (1/0 for specific intervention vs control group), Y=outcome variable (difference score T2-T0b of the primary outcome measure), and Z=mediator:

a: X regressed on Z.b: Z regressed on Y;c’: direct effect of X on Y.

For each experimental intervention, the starting model will consist of all the significant primary mediators of Step 6 that have also been assessed in the control group. In other words, the factors that have shown to be mediators in the correlated growth model will be the starting point for this model. The models will then be complemented with the secondary mediating factors described in Textbox 2. Mediating factors for which the indirect effect (a × b) is insignificant will be removed stepwise, after which a final model will be created.

Model fit, standardized path coefficients—including indirect effects—and the total effect of at least the first and final models will be reported with 95% confidence intervals.

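### Physical activity and four exploratory mediators are not measured when former controls start their intervention, and Step 7's outcome ends before that intervention begins, yet Steps 6 and 7 pool these records

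*Protocol article*

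**What the plan says.** Under Methods, Design, control participants are offered AAF or eMBCT after T2, by preference for all but the first four, and are then followed at Mi', T1' and T2'. Step 6 combines first-semester data with data from the preferentially assigned second-semester participants, and Step 7 also uses both semesters.

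The article presents Table 2 as the full schedule for mediating factors. It gives:

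- **Physical activity** ("Accelerometer: ProMove 3D [52]. Both summative PA and daily PA decline will be considered"): T0b, weeks 3, 6 and 9, and T1/T1'. The T2/T2' and T3 cells are blank.
- **Self-efficacy on activities, catastrophizing, fear of recurrence, causal attributions:** T0b and T1/T1' only.
- **Mindfulness, sleep quality, sense of control, perceived physical activity, fatigue severity:** T2 is included.
- **Repeated at second allocation:** only T0c', for credibility and expectancy.

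Footnote c adds: "All physical activity measurements are blind except for the experimental activity feedback condition at M3, M6, and M9". It removes M3', M6' and M9' activity for second-semester eMBCT. The Design section goes further and says that former controls who choose eMBCT "do not wear the accelerometer during the second semester".

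Step 7 fits one model per intervention, with X=1 for the intervention and 0 for control, and "Y=outcome variable (difference score T2-T0b of the primary outcome measure"). Z is called only the mediator. Textbox 2 words these four factors as changes, decreases or increases, and labels them exploratory.

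**The concern.** For a former control, T2 is the scheduled assessment closest to the start of the intervention. Factors measured there have a usable start value; these five do not. The latest earlier value, T1, closes the control period. A difference T1' minus T1 therefore spans an untreated interval of about 15 weeks as well as the treated one, and T1' minus T0b spans about 26 untreated weeks.

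Physical activity matters most, because Textbox 2 names it as the specific mediator for AAF. The second-semester AAF series starts at M3', when feedback is already running. First-semester AAF slopes start from a blinded T0b measurement. Pooling the two gives a slope factor that means different things in different records.

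The outcome in Step 7 has a related flaw. For a former control, T2 minus T0b is the change under the psycho-educational emails. If that record is coded X=1, control-period change is counted as treatment change.

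**Working it through.** **1. Reproducing the article's figures (Power Analyses)**

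Inputs: "We expect to be able to include 330 eligible participants within a period of 2 years"; "An estimated attrition of 30% of the participants during both experimental interventions and 15% during the minimal intervention control condition"; "Again, we expect a dropout rate of 30% during the second semester".

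- Per arm: 330 / 3 = 110.
- Experimental arms at T2: 110 × 0.70 = 77 each.
- Control arm at T2: 110 × 0.85 = 93.5, stated as 94.
- Second-semester completers: 94 × 0.70 = 65.8.
- Per intervention over both semesters: (2 × 77 + 65.8) / 2 = 219.8 / 2 = 109.9, stated as 110.
- After the 10% exclusion: 219.8 × 0.90 = 197.8, stated as 198.

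The stated figures reproduce.

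**2. Share of treated records from the second semester**

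- Overall: 65.8 / 219.8 = 29.9%. A uniform 10% exclusion leaves this unchanged.
- With the attrition inputs varied by assumption (20–40% experimental, 10–25% control, 20–40% second semester), the share runs from 22% to 38%.
- Per intervention it depends on preference, which the article does not forecast:

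| Assumed share choosing AAF | Second-semester AAF | Share of AAF records | Second-semester eMBCT | Share of eMBCT records |
|---|---|---|---|---|
| 30% | 19.7 | 20% | 46.1 | 37% |
| 50% | 32.9 | 30% | 32.9 | 30% |
| 70% | 46.1 | 37% | 19.7 | 20% |

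**3. Age of the available earlier values**

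T1 falls at about week 9 + 2 = 11 and T2 at about week 26. T1 is therefore 26 − 11 = 15 weeks before T2, and T0b about 26 weeks before it. These are nominal times.

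**4. What each step is left with**

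- **Step 6** tests primary mediators only, so of the five factors only physical activity is affected. Former controls on AAF have M3', M6', M9' and T1': a slope can be fitted, but it has no anchor before feedback and omits weeks 0 to 3. Former controls on eMBCT have no second-semester activity data, so for activity the between-group slope comparison (subhypothesis 4) rests on first-semester eMBCT records.
- **Step 7** is where the four secondary factors enter. If Z is a change, as Textbox 2 implies, a former control's T1' can be set only against T1 or T0b. Physical activity has the same problem if it survives Step 6.

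**5. Step 7 outcome read literally**

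Let the true effect on Y be d, and let a fraction p of X=1 records carry control-period change. If former controls changed during the control period like the control group as a whole, the expected X=1 minus X=0 contrast is (1 − p) × d + p × 0. With p = 0.30 this is 0.70d, a dilution of about 30%. In a single intervention's model, p from 0.20 to 0.37 gives 0.80d to 0.63d.

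**The case against.** A reader might infer that these factors have no value at all before the second-semester intervention, and that change cannot be derived. The documents do not support that. Former controls have all five factors at T0b and T1, and physical activity at M3, M6 and M9 as well. What is missing is a value at the start of treatment.

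A reader might also infer that the AAF activity slope is biased towards zero. That would require most of the response to come before week 3, and the article says nothing on this. The planned 77 first-semester AAF completers keep their T0b anchor. What can be said is that the two slopes are different quantities, not which way the pooled one errs.

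Further points stand in the plan's favour. The missing second-semester eMBCT activity is a disclosed choice, and eMBCT is mainly a comparator for an AAF-specific mediator. The four secondary factors are exploratory. Step 7 does not define Z as a change score. Fatigue is measured at both T2 and T2', so no outcome data are missing: T2' minus T2 is the natural analogue and may be what was intended. The article describes its analysis plan as general in its terms. Figure 3, whose legend lists physical activity, is not shown and might mark another measurement, though neither the text nor Table 2 gives one.

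These points narrow the concern but do not remove it. Both steps pool the semesters without saying which start value applies, and the one outcome definition given is wrong for second-semester records.

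**Conclusion.** The point holds in limited form. For physical activity and four exploratory secondary mediators, no measurement is scheduled at the start of the second-semester intervention, although Steps 6 and 7 use those records. They make up about 30% of treated completers on the article's own figures. The share within each intervention is 20% to 37% if 30% to 70% of former controls choose AAF; an even split is an assumption.

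In Step 6 only physical activity is affected. In Step 7, T2 minus T0b applied to second-semester records assigns control-period change to X=1. The dilution of about 30% holds only if the definition is followed literally and former controls changed like the whole control arm.

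The Design section and Table 2 also disagree on second-semester eMBCT. The first rules out any accelerometer wear; the second lists activity at T1' and its footnote removes only M3', M6' and M9'. These need reconciling.

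The primary effectiveness question uses first-semester data only and is not touched.

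**What to change.** 1. **Controls who have not reached T2.** Add the four secondary mediators to the T2 web questionnaire: 13 + 9 + 2 + 1 = 25 items already in use. For those choosing AAF, take one blinded accelerometer week before feedback starts, with the same device. Recruitment runs to April 2015, so the last controls reach T2 about six months later. Cost: a minor amendment and slightly more participant burden.
2. **Controls already past T2.** Base the main mediation analysis of these five factors on first-semester records. Use the second-semester M3' to T1' activity series only in a sensitivity analysis. Cost: fewer records for these factors, in a mediator analysis already planned at 198 against the 254 from the article's own conventional calculation.
3. **Definitions.** State that for second-semester records Y is T2' minus T2 and mediator change is taken from T2. Cost: wording only, if settled before the mediation analysis.
4. **Schedule.** Reconcile the Design section with the T1' activity entry in Table 2 and footnote c for second-semester eMBCT. Cost: wording only.

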#### Mediating Factors

Several categories of mediators will be considered: intervention-specific mediators for either eMBCT (eg, mindfulness, catastrophizing, and fear of cancer recurrence) or AAF (eg, physical activity, perceived physical activity, and self-efficacy on physical activity), and generic mediators (eg, sleep quality, sense of control over fatigue, credibility, expectancy, working alliance, and causal attributions). Furthermore, a distinction is made between primary and secondary mediating factors: primary factors are assessed at multiple occasions during the intervention in order to study the timely development of those factors; secondary factors are not assessed during the intervention. A complete overview of all assessments on mediating factors is given in Table 2.

#### Demographics, Medical History, and Control Factors

Several other factors are assessed, including demographics, medical history, and control factors. All are listed in Table 3.

### Analysis Plan

#### Overview

SPSS software will be used for data management and Mplus [79], which is a latent variable modeling program, for the subsequent analyses. The exact versions of the software used will be reported in the future papers.

#### Pre-Analysis

##### Power Analyses

The sample size for analyses for data relating to the primary objective has been calculated for a repeated measures analysis of variance: based on an alpha of .05, a minimal detectable effect size of f2=.15, and a power of .80, a total number of 55 participants [80] is required in each group to answer the primary research question of this study in a statistically valid manner.

We expect to be able to include 330 eligible participants within a period of 2 years, based on a mean of 3.7 intakes per week for the eMBCT of the Helen Dowling Institute in 2011. An estimated attrition of 30% of the participants during both experimental interventions and 15% during the minimal intervention control condition [51] would leave us with 77 participants in each experimental group and 94 participants in the control group at T2. Again, we expect a dropout rate of 30% during the second semester. Such a dropout would leave a total of 110 participants completing each experimental intervention. Ten percent of the participants may have to be excluded from the analyses because of recurrence or diagnosis of metastasis. That would result in 198 participants that complete the full trial. We expect that this number will be enough for testing the 6 mediating factors or effect predictors: A classical, conservative power calculation (analysis of variance for testing 6 mediators or effect predictors with an intermediate effect size (f2=.08), corrected according to Bonferroni (alpha=.05/6), and at a power of .80 [81]) would result in approximately 254 participants being needed. We expect that the actual power when including 198 participants, and not the required 254 participants, will be great enough to detect up to 6 mediators or effect predictors with the use of Bayesian statistics [76]. Bayesian statistics allow analysis on small sample sizes [76,77], as more power can be generated with the use of prior information which is incorporated in the model that is being tested. Various papers describe comparisons between traditional null hypothesis testing and Bayesian estimation [82-85]. For this study, prior knowledge is available for many parameters, such as the effects of mindfulness in cancer survivors [23,25,66,86] and the role of working alliance in online interventions [87]. Examples of these methods can be found in both applied psychology and social science articles [88-92].

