## Results

Recruitment for the trial started in March 2013 and is expected to continue until April 2015. No major changes have been made to the protocol. However, due to an error in the randomization algorithm between January 14, 2014, and July 15, 2014, allocation was dependent on the number of participants who were allocated at once. This in turn was completely random. Consequently, 10 participants were allocated directly to the AAF group; 4 other participants were divided equally between the 2 experimental interventions; and 15 accounts (of which, 1 was a dummy account) were equally divided between the 3 groups. None of the researchers were aware of this error, as this allocation could very well have simply been the result of the “roll the dice” scenario that should have been applied. How many participants were allocated at once was not the subject of the researchers’ decision-making. Therefore, we argue that allocation has still been random and, accordingly, data for all considered participants will be processed as originally planned.

At the time of this writing in January 2015, 269 patients have registered at the project website. Of these, 111 have been officially included in the study, 50 were excluded from participation, and 35 withdrew before their eligibility was checked. The remaining patients are still in the enrollment phase. The main reason for exclusion so far has been a score lower than 35 on the CIS fatigue severity subscale (60%). Furthermore 11% did not meet the psychiatric stability requirement, 8% were younger than 18 at the time of cancer diagnosis, and 8% were still receiving cancer treatment.

Current group sizes as of January 2015 for participants in the first semester are 36 (AAF), 24 (eMBCT), and 32 (control). However, 19 participants have not yet been randomized. Initial responses to the primary research question are expected to be available by the end of 2015.

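### The stated 55 per group does not follow from f2=.15, alpha .05 and power .80, and the 330 target with its derived numbers is no longer attainable on the article's own counts

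*Protocol article*

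**What the plan says.** Protocol article, Power Analyses: the size for the primary objective comes from a repeated measures ANOVA calculation with alpha set to .05. The result reads "a minimal detectable effect size of f2=.15, and a power of .80, a total number of 55 participants [80] is required in each group". The number of occasions and the within-person correlation are not given.

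The same section continues: "We expect to be able to include 330 eligible participants within a period of 2 years". With 30% attrition in the experimental arms and 15% in control, it expects 77, 77 and 94 participants at T2. With 30% dropout in the second semester, it expects 110 completing each experimental intervention. After 10% exclusion, 198 complete the full trial. It sets that 198 against about 254 from its own classical calculation for six mediators or effect predictors, and argues that Bayesian estimation will cover the difference.

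Protocol article, Results: "Recruitment for the trial started in March 2013 and is expected to continue until April 2015". In January 2015, 269 had registered. "Of these, 111 have been officially included in the study, 50 were excluded from participation, and 35 withdrew before their eligibility was checked". Group sizes were 36, 24 and 32, with 19 not yet randomised. The section reports no major protocol change and does not revise the target.

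**The concern.** A sample-size sentence fixes what the trial claims to be able to detect. If n, effect size and power do not belong together, a reader cannot tell which effect a null result would speak against. The value f2=.15 corresponds to d of about 0.775 for two equal groups, whereas 55 per group would detect d of about 0.54 with 80% power. These are different claims.

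The second issue is that the Power Analyses section still rests on 330 participants, while the Results section reports about a third of that number (111/330 = 34%) with some three to four months of recruitment left. The Discussion says that the methods are fixed in advance so that later papers can be judged against them. Later papers would then be judged against a power basis that no longer applies. This matters most for the mediator and predictor analyses, whose expected 198 was already below the calculated 254.

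**Working it through.** **Inputs.** Power Analyses: alpha .05, f2=.15, power .80, 330 planned, attrition 30% and 15%, exclusion 10%. Randomization: three arms with equal probability. Results: 269 registered, 111 included, 50 excluded, 35 withdrawn. Two-sided tests are assumed.

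**1. Reproducing the 55.** F-test power uses a noncentral F distribution with noncentrality f2 × N.

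| Test at f2=.15, alpha .05 | N for power .80 | Power at 55 per group |
|---|---|---|
| 1 df (two-group contrast) | 55 in total (power 0.805) | 0.98 (N=110) |
| 2 df (three groups) | 68 in total | 0.996 (N=165) |

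With equal groups this is 28 per group (two groups) or 23 per group (three groups).

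**2. Can the unstated repeated-measures inputs rescue it?** Standard between-group and interaction tests were tried with 2 or 3 groups; 2, 3, 4 or 7 occasions; and correlation 0 to 0.8. They need at most 25 per group and about 61 in total (63 = 3 × 21 with equal groups). The most conservative form keeps the noncentrality at f2 × N and uses the interaction degrees of freedom. It needs at most 46 per group with two groups (92 in total) or 40 per group with three (120 in total). None gives 110 for two groups or 165 for three. Values near 55 per group appear only with a smaller alpha (for example 54 at alpha .025, two groups, seven occasions, conservative form), which contradicts the stated .05.

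**3. Candidate explanations.**
- A total was read as a per-group number: 55 in total for 1 df. A three-group between-factor test with two occasions and correlation 0.5 also gives 54 in total.
- The effect size was mislabelled: f=.25 (f2=.0625) with three groups gives 53 per group.

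The article does not allow a choice between them.

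**4. What 55 per group detects.** d = 2 × √f2 = 2 × √.15 = 0.775. A two-sample t test with 55 v 55, two-sided .05 and power .80 detects d = 0.54, so f2 = 0.539²/4 = .073.

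**5. The plan's chain reproduces from 330.** 330/3 = 110; 110 × 0.70 = 77; 110 × 0.85 = 93.5, or 94. Per experimental intervention over both semesters: 77 + (94 × 0.70)/2 = 109.9, or 110. Then 2 × 110 × 0.90 = 198.

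**6. Accrual.** The abstract dates the start to April 2013 and the Results to March 2013, so 111 were included in 21-22 months, or 5.0-5.3 per month. Carried to April 2015 this gives about 126-132, which is 38-40% of 330. Pending: 269 − 111 − 50 − 35 = 73. If all enter: 111 + 73 = 184, which is 56% of 330.

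**7. Analysable completers, three equal arms.**

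| Total included | Per arm randomised | Experimental (× .70 × .90) | Control (× .85 × .90) |
|---|---|---|---|
| 126-132 | 42-44 | 26.5-27.7 | 32.1-33.7 |
| 184 | 61.3 | 38.6 | 46.9 |

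An extreme case adds about 38 new registrants and includes everyone: 222, or 74 per arm. That gives 74 × 0.70 = 51.8 experimental completers at T2 before the 10% exclusion.

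**8. Detectable effect and power, unadjusted t test.**

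| Arms | d at 80% power | Power at d=0.775 |
|---|---|---|
| 27 v 33 | 0.74 | 0.84 |
| 39 v 47 | 0.61 | 0.94 |

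**9. The 198.** Scaling by inclusions: 198 × 184/330 = 110; 198 × 126/330 = 76 and 198 × 132/330 = 79; even 198 × 222/330 = 133.

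**The case against.** - **The error is conservative.** If f2=.15 is the intended target, 55 per group is more than enough, and even the projected arms keep power at 0.84-0.94. This stands. A reader might infer that the trial is underpowered for its stated effect, and the figures do not support that. They show that the stated effect, n and power do not belong together.
- **The cause is unknown.** A reader might infer that 55 is simply the total N misplaced. That is one candidate, and a mislabelled f=.25 fits about as well. Only the failure to reproduce is established.
- **The shortfall against 55 is a projection.** It holds for experimental-arm completers in every scenario examined. It need not hold for numbers randomised, which reach 61 per arm if all pending registrants enter. The planned analysis is an intention-to-treat growth model that uses partial data.
- **The t-test figures do not match the planned model.** This is correct. The model uses baseline and repeated measures. With an assumed baseline-outcome correlation of .5 to .7 (not in the article), multiplying by √(1 − r²) lowers the detectable d to 0.64-0.53 (27 v 33) and 0.53-0.44 (39 v 47).
- **Table 1 does not rule out d=0.775.** A reader might infer that f2=.15 cannot serve as a target because 0.775 exceeds every point estimate in Table 1 (0.05-0.61). Four upper confidence limits exceed it (0.92, 1.02, 0.90, 0.88), and the accompanying text warns that the pooled effects may not represent interventions aimed at fatigue.
- **Accrual is disclosed, and 330 was an a priori figure.** True. But the Results give counts without saying that the target and the numbers built on it will be missed.

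**Conclusion.** Two corrections are warranted. First, 55 per group does not follow from f2=.15, alpha .05 and power .80. The standard calculations need 55 in total (1 df) or 68 in total (three groups), and no repeated-measures variant tried at alpha .05 comes up to 55 per group. The statement either requires about twice as many participants as its effect size needs (55 against 28 or 23 per group) or names the wrong effect. The source cannot be determined from the article.

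Second, the shortfall against 330 is beyond reasonable doubt on the reported counts, and the derived 77, 94, 110 and 198 fall with it. The projected 27-39 experimental completers and 33-47 controls assume linear accrual or full entry of pending registrants, equal arms, and the plan's own attrition and exclusion rates. The detectable d of 0.61-0.74 is unadjusted, so it is an upper guide for the growth model. The analysis itself is unaffected. What is wrong is the statement of what the trial can show.

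**What to change.** - Restate the primary sample-size sentence with the test named and n paired with the effect it detects. For example: 55 analysed per group gives 80% power for d of about 0.54 in each intervention-control contrast, two-sided .05, unadjusted. If f2=.15 is the intended target, give the smaller n that belongs to it.
- Keep 330 as the a priori target, and add that it will not be reached. Give the projected analysable numbers (about 27-39 per experimental arm, 33-47 controls) and their detectable effect (d about 0.61-0.74 unadjusted, smaller under the growth model, which uses baseline, repeated measures and partial data).
- State that the 198 relied on for the mediator and predictor analyses will not be reached.

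The cost is text only. The stated figures become less favourable, and no extra patients are needed.
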